#### Blinding

Although we will try to blind patients, therapists, and assessors it is unlikely that patients and therapists will stay blind during the course of this study due to the nature of the applied treatment. However, to make sure that the risk of bias stays low, patients will be registered in the database by means of a patient ID code so assessors are blinded during analysis. Only the primary investigator will have knowledge regarding allocation.

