**Methods and design:**

An assessor-blinded randomized controlled trial will be conducted in patients with impaired trunk control after stroke. A total of 60 patients will be randomly allocated to the control or the experimental group by means of sealed opaque envelopes. They will receive either 16 h of additional trunk exercises (experimental group) or cognitive exercises (controls) for 1 h a day, 4 days a week for 4 weeks. Patients will also receive 2 h of standard care consisting of physiotherapy and occupational therapy. Gait performance will be assessed clinically by the Tinetti Test and biomechanically by means of a full body gait analysis. In addition, the effect of the exercise protocol on the trunk itself and trunk activities of daily living will be assessed by the Trunk Impairment Scale and the Barthel Index.

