## Methods and design

### Study design and setting

The design of this study is a 4-week, assessor-blinded randomized controlled trial with a 1-month follow-up at an established rehabilitation hospital. Participants will be randomly allocated to either the experimental or the control group by simple randomization executed by an independent researcher who is not involved in the assessment or treatment of the patients. After participants agree to participate in this study, the independent researcher will draw one of the 60 envelopes (30 for each group) and will assign the participants to the allocated group. Patients will be recruited from the stroke population of the rehabilitation hospital RevArte, located in Edegem (Antwerp, Belgium). This rehabilitation hospital is a 194-bed facility and is able to offer inpatient and outpatient rehabilitation for approximately 300 patients at the same time. All participants will receive 16 h of either trunk or cognitive exercises in addition to the multidisciplinary standard care stroke rehabilitation program provided by the rehabilitation staff.

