Thirdly, reflective markers will be placed on bony anatomical landmarks according to the standard Plug-In-Gait model combined with a more detailed spine model developed and assessed for reliability by Heyrman et al. (2013) [27]. These two models allow the computation of linear and angular displacements of the different body segments. Although, good intra-protocol repeatability has been established for the Plug-In-Gait model, variability due to differences in marker placement has shown to be the major contributor to overall variance [28, 29]. Therefore, a standardized protocol was implemented whereby bony landmarks were located by manual palpitation by the primary investigator. To diminish artefacts, the motion trackers were firmly affixed to the skin with double-sided tape. Reflective markers for the Plug-In-Gait model of the upper body are located at the front and back of the head (left and right), the processus spinosus (PS) of the seventh cervical vertebrae, the PS of the tenth thoracic vertebrae, the jugular notch of the sternum, the xiphoid process of the sternum, the left and right acromioclavicular joints, the left and right points of rotation of the elbow, the styloid process of the left and right ulna and radius, and on the dorsum of both hands just below the second metacarpals. Reflective markers for the Plug-In-Gait model of the lower body are located on the left and right spina iliaca anterior superior and spina iliaca posterior superior, the left and right points of knee rotation, the left and right lateral malleoli, the second left and right metatarsal heads, and the left and right calacanei. Reflective markers for the spine model are located on the PS of the second and sixth thoracic vertebrae, and the PS of the first, third, and fifth lumbar vertebrae. Four markers are attached at one third of the length of the femur and fibula in alignment with trochanter major, the rotation point of the knee, and the lateral malleolus to examine the presence of rotation in the lower limbs (Fig. 2).

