#### Post-treatment assessment and follow-up

Immediately after the intervention and 1 month post intervention, patients will again be subjected to a clinical and biomechanical assessment to examine treatment effect and the treatment effect sustainability.

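### The marker-based gait outcomes are not assessor-blinded as written: the primary investigator knows allocation and locates the marker landmarks

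*Protocol article*

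**What the plan says.** The label appears twice. The Abstract has "An assessor-blinded randomized controlled trial will be conducted in patients with impaired trunk control after stroke", and Study design and setting has "The design of this study is a 4-week, assessor-blinded randomized controlled trial".

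The Blinding section opens with an intention ("Although we will try to blind patients, therapists, and assessors") and concedes that patients and therapists will probably not stay blind. It then names its safeguard: "patients will be registered in the database by means of a patient ID code so assessors are blinded during analysis". It closes with "Only the primary investigator will have knowledge regarding allocation".

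The marker-placement text under Baseline assessment explains why one operator is used: "variability due to differences in marker placement has shown to be the major contributor to overall variance". For that reason, "bony landmarks were located by manual palpitation by the primary investigator".

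Post-treatment assessment and follow-up says that straight after the intervention and 1 month later "patients will again be subjected to a clinical and biomechanical assessment".

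**The concern.** Patients and therapists cannot be kept blind here, so assessor blinding is the main remaining protection against detection bias. The article gives the label to the whole trial. It also gives one person both knowledge of the group and a hand in the measurement, at the step it regards as the largest source of variability in the gait model. If that holds after treatment, a group difference in trunk or center-of-mass kinematics could not be defended as a blinded finding.

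A second, weaker worry concerns the clinical scales. A code in the database hides the group from someone processing files. It does nothing for a rater who is in the room with a patient who knows which exercises he or she has been doing.

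**Working it through.** The article gives no figure to reproduce. The check is a side-by-side reading, followed by a count of what is exposed.

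**Marker-based outcomes**

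1. Who knows the group: the primary investigator (Blinding).
2. Who locates the landmarks: the primary investigator (Baseline assessment). The text says located rather than placed. Since the aim is to reduce differences in marker placement, the person who finds the landmark in effect fixes the marker position.
3. When: at baseline, and again in the biomechanical assessments after treatment and at 1 month. No other operator is named for the later visits.
4. Result: after allocation, a person who knows the group takes part in the measurement. This contradicts the label.

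**What is exposed**

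- Table 2 lists three kinematic rows: trunk range of motion, trunk displacements and center-of-mass displacements. Each is measured at baseline, post and follow-up. Two of the three occasions fall after allocation.
- The spatiotemporal parameters are less exposed. Gait events come from ankle marker trajectories together with force plates.
- The EMG outcomes do not depend on these landmarks.
- With 60 patients and two post-baseline visits each, 60 × 2 = 120 gait assessments are planned after allocation. Current study status reports 28 recruited, so 60 − 28 = 32 patients, or 32 × 2 = 64 assessments, can still be protected in full. The other 28 × 2 = 56 belong to patients already recruited. The article does not say how many of those had taken place.

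**Clinical scales**

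The primary investigator's only stated scoring of a clinical scale is the Trunk Impairment Scale and Functional Ambulation Categories at eligibility screening. That is part of establishing eligibility and is not a breach. No section names the post-baseline rater of the Tinetti Test, Trunk Impairment Scale or Barthel Index. The safeguard that is described acts at analysis, which comes after the scoring.

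**Who knows allocation, section by section**

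- Study design and setting: an independent researcher, outside assessment and treatment, draws the envelope and assigns the patient. That person must know the group.
- Allocation: the allocating person is a blinded investigator using envelopes stored elsewhere.
- Blinding: the primary investigator alone knows.
- Discussion (limitations): therapists and patients cannot be blinded, so they know as well.

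These four statements cannot all be true as worded.

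**The case against.** The strongest reply is that the Blinding section cuts both ways. If only the primary investigator knows the group, the assessors do not. Data collection and management treats assessors as a separate, trained group, with the primary investigator kept informed and consulted. A reader might infer from the label's failure that the Tinetti Test is scored by someone who knows the group. The documents do not support that, and this part of the objection stands in full. The patient code is also not the only protection: knowledge of allocation is restricted, the envelopes are kept off site, and the independent researcher is kept out of assessment and treatment.

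It can also be said that a journal article may leave to the full protocol who rates which scale and how patients are told not to disclose. That is fair, and the missing detail is not the complaint. What remains is that the article does state a mechanism, and the stated mechanism cannot do what is asked of it at a face-to-face visit.

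On the markers, the palpation sentence sits under the baseline heading and is in the past tense. Its repetition after treatment is inferred from the statement that the assessment is done again. The inference is natural, but it is an inference. The remark about variance concerns differences between placements and is given as the reason for standardizing. It does not show a shift in favor of one arm.

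**Conclusion.** The point holds for the marker-based kinematic secondary outcomes: as written they are not assessor-blinded at the post-treatment and 1-month visits. This rests on three assumptions:

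- The primary investigator also locates the landmarks at those visits.
- Locating the landmark determines marker position.
- The knowledge of allocation is already held at that time.

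Each is the plain reading, and none is contradicted elsewhere.

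For the Tinetti Test, Trunk Impairment Scale and Barthel Index the conclusion is limited. The described code does not protect the scoring, and the text does not establish that any rater knows the group.

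No size in scale points or degrees can be given. Any figure for a shift in the Tinetti Test would need an invented degree of leniency and an unblinded rater whom the article does not show. Nor do the documents show that bias has occurred. They show that the stated protection does not cover these outcomes.

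The statement that only one person knows allocation must also be corrected, because it conflicts with Study design and setting, Allocation and the Discussion.

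**What to change.** - For patients still to be allocated, let the independent researcher hold the allocation list and disclose it only to the treating therapists. The primary investigator can then go on locating landmarks without knowing the group, and the benefit of a single operator is kept.
- State that whoever scores the Tinetti Test, Trunk Impairment Scale or Barthel Index, or places markers after baseline, does not know the group at the visit. Do not rely on the database code as the mechanism for this.
- Reconcile Study design and setting, Allocation, Blinding and the marker text, so that they agree on who assigns, who knows and who measures.
- Flag post-baseline gait assessments made with knowledge of allocation, and run a sensitivity analysis of the kinematic outcomes without them. Later blinding cannot repair assessments already made among the 28 patients recruited.
- If the primary investigator is to stay unblinded and keep placing markers, limit the assessor-blinded label to the outcomes it covers.

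The cost is a change of wording and of who holds the list. The independent researcher and the trained assessors already exist. There is one small drawback: questions or problems that need knowledge of the group must go to someone other than the primary investigator.

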### Outcome measures

#### Primary outcome measures

Gait performance as measured clinically via the TT is the primary outcome measure. The FAC will not be used as an outcome measure to assess gait performance as it is a more descriptive clinical measure and less detailed compared to the TT. The TT measures gait and balance using a 2- or 3-point ordinal scale with scores ranging from 0 to 1 or 2. The maximum score of the total TT is 28 points, whereby a maximum of 12 and 16 points can be obtained for gait and balance subscales, respectively. Nine items, such as sit to stand, standing balance with eyes open and eyes closed, turning 360° and sitting down, are assessed on the balance subscale. The gait subscales assess eight items ranging from step length, step symmetry, foot clearance, and step width. Reliability and validity of the TT for stroke patients have been reported (ICC2,1 = 0.84; TT-FIMmotor *r* = 0.55; TT-gait speed *r* = 0.82) [39]. The minimal clinically important difference of the TT is 7 points (area under the curve (AUC) = 0.743) and a minimal detectable change of 6 points [39].

#### Secondary outcome measures

Several outcome measures will be assessed during biomechanical gait analysis. Firstly, the following spatiotemporal parameters will be assessed: percentage (%) of stance time, % of swing time, % of single support time (SS), % of double support time (DS), stride time, step time, stride length, step length, step width, walking speed, and cadence. Secondly, kinematic parameters, which describe the displacements and/or range of motion (ROM) of the segments in the sagittal, frontal, and transversal planes, will be assessed. Kinematic parameters across the entire gait cycle will be examined by means of 1D Statistical Parametric Mapping (spm1d). Subsequently, horizontal and vertical displacements of the center of mass (COM) will be analyzed during right and left strides. Lastly, the normalized integrated linear envelope of the EMG signal will be computed, making it possible to observe both muscle timing and amplitude simultaneously. Raw EMG data will be rectified to obtain absolute values of the signal. Thereafter, the linear envelop, integrated EMG and normalized EMG, will be acquired by computing the outline of the signal, the AUC and calculating the average EMG signal throughout the gait cycle for every subject, respectively. EMG activity across the entire gait cycle will be examined by means of spm1d statistics. Muscle activity of the back, abdominal, and lower limb muscles will be registered. Two trials with a sufficient number of strides from each condition will be selected for analysis.

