**Fig. 2 Fig2:**
[figure not shown]
Plug-In-Gait model (*black*) and spine model (*white*)

Finally, EMG sensors will be attached to the surface electrodes. The signal-to-noise ratio will be checked to ensure clear EMG recordings.

When preparation is complete, a static calibration will be performed with the knee alignment device (KAD) to avoid knee joint angle cross-talk. Patients are asked to stand still in the middle of the force platform with arms outstretched and thumbs facing down. The KAD will be placed at the rotation axis of the knee. To ensure minimal cross-talk the KAD will be replaced three times by two different investigators. During analysis the most optimal placement of the KAD will be chosen to analyze the dynamic walking trials. Subsequently, the patients will have to walk barefoot at their natural, self-selected speed and without walking aid or orthosis, if possible, over a 12-m walkway and supervised by a skilled physiotherapist in order to avoid falls or other problems. To ensure the patient’s safety during walking, a safety harness can be worn which will not limit trunk movement. In total, a minimum of six walking trials will be recorded. Of these six trials, three will consist of clean heel strikes onto the force platforms from the right stride and three from the left so that kinetic parameters can be analyzed.

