### Sample size

Analysis was based on results of a previous randomized controlled trial concerning the effect of additional trunk exercises on the TT and TIS that was carried out by our research group [7]. Saeys et al. (2012) [7] reported a change score of the TT of 13.45 and 5.2 points for the experimental and control groups, respectively. The number of patients required for this study was calculated a priori to ensure sufficient statistical power. Analysis showed that a sample size of 30 patients in each group, 60 in total, was necessary to detect a difference with 80% using a two-tailed hypothesis (with significance level of *p* = 0.05).

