## Discussion

The aim of this study is to further explore the effects of additional customized trunk exercises on clinical and biomechanical gait performance. Despite the evidence demonstrating the importance of trunk control after stroke, studies about the effects of trunk rehabilitation on gait performance are inconsistent. The findings of this study might lead to new scientific insights into the importance of the trunk during gait rehabilitation in people suffering from stroke submitted to a rehabilitation hospital. Since clinical improvements are of greater importance to patients and physiotherapists as they assess functional tasks and are easier to use in a clinical setting, the TT and its subscales will be the primary outcome measures. Subsequently, a variety of biomechanical parameters collected by a full body gait analysis will be our secondary outcome measures. However, it is still important to consider the effect of this training program on the trunk itself and on ADL as this is the main focus of the training program. Because of this, the TIS and BI will assessed as tertiary outcome measures.

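### The biomechanical analysis uses two trials per undefined 'condition' out of at least six recorded, with no reproducible selection rule; this gives up some precision on secondary outcomes

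*Protocol article*

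**What the plan says.** The gait procedure is in the protocol article under Procedures, Baseline assessment (text after Fig. 2). Patients walk barefoot at one self-selected speed, and "In total, a minimum of six walking trials will be recorded". Of these, "three will consist of clean heel strikes onto the force platforms from the right stride and three from the left". The stated purpose of the clean strikes is to allow kinetic analysis. The same assessment is repeated after treatment and one month later (Post-treatment assessment and follow-up; Table 2).

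The paragraph on Secondary outcome measures covers spatiotemporal, kinematic, centre-of-mass and EMG outcomes and ends: "Two trials with a sufficient number of strides from each condition will be selected for analysis". The sentence comes directly after the EMG text.

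On who sees what, the Blinding section says "patients will be registered in the database by means of a patient ID code so assessors are blinded during analysis" and "Only the primary investigator will have knowledge regarding allocation".

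On the rank of these outcomes, the Discussion says "a variety of biomechanical parameters collected by a full body gait analysis will be our secondary outcome measures". The Tinetti Test is primary.

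**The concern.** The protocol secures at least six trials per session and then restricts how many enter the analysis, without giving a reason. This is a stated rule rather than a detail left open: a later analysis plan that used every trial would depart from it.

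The rule also cannot be applied the same way by two people. Only one walking task is described, so 'condition' has no clear referent. It could mean the session (two of six trials) or the side (two right and two left, so four of six). 'Sufficient' has no threshold, and no order or tie-break is given for trials that all qualify.

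At stake is the precision of the biomechanical outcomes, which make up the whole secondary tier and which the Discussion presents as a strength of the trial. With 60 patients, averaging trials that are already recorded is an inexpensive way to reduce noise.

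**Working it through.** **The plan's own figure.** The article states no precision target for the biomechanical outcomes. Its only sizing statement is for the Tinetti Test: "sample size of 30 patients in each group, 60 in total, was necessary to detect a difference with 80% using a two-tailed hypothesis", at a "significance level of *p* = 0.05". The change scores quoted there differ by 13.45 − 5.2 = 8.25 points. Thirty per group at 80% power then implies an SD of about 11.4 (normal approximation) or 11.2 (t-test). No SD is stated, so the figure can be neither confirmed nor refuted, and it does not bear on this point.

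**How open the choice is.** If two of six trials are taken, there are C(6,2) = 15 possible sets per session. If two of three per side are taken, there are C(3,2) × C(3,2) = 9.

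**Precision: inputs.**
- Trials per session: k = 6, or 3 per side (Baseline assessment).
- Trials analysed: k = 2, in total or per side (Secondary outcome measures).
- Single-trial ICC within a session: not in the document; assumed 0.7 to 0.9.
- Correlation r between visits of a patient's underlying value: not in the document; assumed 0.5 to 0.8.

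**Formulas**, with single-trial variance set to 1:
- Variance of a k-trial mean at one visit: ICC + (1 − ICC)/k.
- Variance of the change between two visits: 2·ICC·(1 − r) + 2·(1 − ICC)/k.

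**Example**, ICC 0.8 and r 0.8:
- k = 2: 2 × 0.8 × 0.2 + 2 × 0.2/2 = 0.320 + 0.200 = 0.520
- k = 3: 0.320 + 0.133 = 0.453, a cut of 12.8%
- k = 6: 0.320 + 0.067 = 0.387, a cut of 25.6%

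**All cases, cut in change-score variance:**

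| ICC | r | k=2 | k=3 | k=6 | Cut, 2 to 3 per side | Cut, 2 to 6 |
|---|---|---|---|---|---|---|
| 0.9 | 0.8 | 0.460 | 0.427 | 0.393 | 7.2% | 14.5% |
| 0.8 | 0.8 | 0.520 | 0.453 | 0.387 | 12.8% | 25.6% |
| 0.7 | 0.8 | 0.580 | 0.480 | 0.380 | 17.2% | 34.5% |
| 0.9 | 0.5 | 1.000 | 0.967 | 0.933 | 3.3% | 6.7% |
| 0.8 | 0.5 | 1.000 | 0.933 | 0.867 | 6.7% | 13.3% |
| 0.7 | 0.5 | 1.000 | 0.900 | 0.800 | 10.0% | 20.0% |

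In patients: 30 per arm analysed on two of six trials are as precise as 30 × (1 − 0.345) ≈ 20 to 30 × (1 − 0.067) = 28 per arm analysed on all six. If two of three per side are used, the equivalent is 30 × (1 − 0.172) ≈ 25 to 30 × (1 − 0.033) = 29.

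**Cross-sectional scale, 2 to 6 trials:** ICC 0.9, 0.950 to 0.917 (3.5%); ICC 0.8, 0.900 to 0.833 (7.4%); ICC 0.7, 0.850 to 0.750 (11.8%). Setting r = 0 in the change formula gives the same percentages, so they are also the lower end for change scores as r falls towards zero.

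**The case against.** **Reading of the sentence.** Two trials per side is a natural reading, because the trials are collected by side and the centre-of-mass outcome is described for right and left strides. The sentence may also govern EMG alone. Both points stand. They halve the gain or narrow its reach, but they also show that the sentence is ambiguous.

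**Size.** The document gives neither ICC nor r. The gait procedure itself names differences in marker placement as the main source of variance for the marker model. Markers are placed afresh at each session, so this error lowers r and more trials do not reduce it. Nor is a change-score model stated: under Statistical analysis, repeated measures ANOVA is assigned to the clinical data and the curves go to spm1d. This stands, which is why the working includes r = 0.5 and the cross-sectional scale. A clean force-plate strike also does not prove that a trial is usable for EMG or trunk motion, so six valid trials is an upper case for a session with the minimum recording.

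**Bias.** A reader might infer that a free choice of trials lets someone favour one arm. The document does not support that. Assessors are blinded during analysis through ID codes, and selection blind to arm adds noise rather than a difference between arms. Bias would be possible only if the primary investigator, who knows the allocation, chose the trials, and the article does not say who chooses. Blinding to visit is not mentioned.

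**Article detail.** Which trials to process is often left to a laboratory procedure or analysis plan, and the article refers to standardised procedures and training. This answers the missing tie-break in part. It does not answer the stated cap of two.

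**Conclusion.** The point holds in a limited form. The article caps the trials analysed below the number recorded, leaves it unclear whether two or four of six are used, and gives no rule that two analysts would apply alike. The direction of the loss is certain for the outcomes the sentence covers; its size is not. The reduction in change-score variance available is about 7% to 35% if two of six are used and about 3% to 17% if two of three per side are used. It is less where session-level marker error dominates. The cross-sectional figure for two to six trials is about 3.5% to 12%. All of these rest on assumed ICC (0.7 to 0.9) and, for change scores, r (0.5 to 0.8).

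Two stronger readings are not supported: that exactly two trials feed every biomechanical outcome, and that the selection biases the comparison of arms. The Tinetti Test and the sample size are unaffected. This is a cheap improvement to secondary outcomes, not a threat to the trial's main conclusion.

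**What to change.** Replace the sentence at the end of Secondary outcome measures with:

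> All technically valid trials recorded at each session will be analysed for each side, and each patient's value or curve is the mean over all valid strides.

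If the number must be limited, state the number per side and take the first valid trials per side in recording order, with validity judged by someone blind to arm and visit. Either wording removes the need to interpret 'condition' and 'sufficient' and should name the outcomes it covers.

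The cost is one sentence of text plus extra marker labelling and signal processing. No new visits or recordings are needed, and the rule can be applied to sessions already recorded.
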